## Abstract

**Introduction:**

Activity-based therapy (ABT) delivers intensive, repetitive sensorimotor stimulation to enhance neuroplasticity after spinal cord injury. ABT has demonstrated synergistic benefits with cervical transcutaneous spinal cord stimulation (tSCS) for motor recovery particularly in individuals with chronic cervical spinal cord injury. However, its efficacy in subacute cases remains an emerging area of research. Accordingly, this study aims to determine the efficacy of an adjunctive ABT paired with cervical tSCS compared with ABT alone on upper limb function in people with cervical spinal cord injury receiving in-patient rehabilitation.

**Methods and analysis:**

This study is a single-centre, double-blind, two-arm randomised controlled trial. We will enrol 40 individuals with cervical spinal cord injury receiving in-patient rehabilitation (20/group). Participants will be randomly assigned to an intervention group (ABT+tSCS) or a control group (dose-matched ABT+sham stimulation). Both groups will receive 45 min of ABT+active or sham tSCS in addition to usual care for 20 sessions, 3 times per week. The primary outcome measures will be the Upper Extremity Motor Score of the International Standards for Neurological Classification of Spinal Cord Injury. Secondary measures will include clinical measures of upper limb impairments and activity limitations and neurophysiological measures (transspinal, motor and somatosensory-evoked potentials). All measures will be taken pre-intervention, post-intervention and at a 1-month follow-up.

**Ethics and dissemination:**

This study was approved by the Research Ethics Committee en réadaptation et en déficience physique of Santé Québec Centre-Sud-de-l’Île-de-Montréal - Universitaire (MP-2024-2080). All procedures will be conducted in accordance with the principles of the Declaration of Helsinki.

**Trial registration number:**

NCT07361627.

STRENGTHS AND LIMITATIONS OF THIS STUDYThis study uses a rigorous control design with an active, dose-matched control group to isolate the specific effects of stimulation.Both participants and outcome assessors are blinded to group allocation to minimise bias.The study protocol was co-designed with individuals with lived experience of spinal cord injury, caregivers and clinicians to ensure clinical and personal relevance.Variability among participants with subacute spinal cord injury may introduce response variability and limit generalisability.

## Introduction

 More than 50% of injuries to the spinal cord occur at the cervical level (ie, tetraplegia), which consequently impacts arm and hand function.^1^ The arm and hand, collectively referred to as the upper limb, play a vital role in interacting with the environment. Following a spinal cord injury (SCI), the onset of spasticity, along with reduced strength, sensation and hand dexterity, limit participation and independence in daily activities and lead to a decreased quality of life.^2^ Regaining upper limb function is consistently identified as one of the most important priorities for people with tetraplegia.^2–4^ Unfortunately, there is a paucity of literature on the effect of training on upper limb function in people with cervical SCI.^5–8^

Activity-based therapy (ABT) is defined as any intervention that combines intense, repetitive and often rhythmical input to the central nervous system.^9^ It aims to stimulate neuromuscular changes through repeated activation of neuronal networks located above and below the injury and is considered an evidence-based intervention for people with SCI.^10
11^ ABT involves task-specific practice using external stimuli and cognitive functions, exercise progression and feedback provision, which can foster motor recovery.^12
13^ In a qualitative study, people with spinal cord injuries perceived that ABT can support neurological recovery, enhance physical and mental well-being, foster independence and instil hope.^14^

Although effective, ABT remains an indirect method of activating the nervous system. Recent advances in non-invasive electrical stimulation techniques enable the direct modulation of neuronal activity in the brain, spinal cord or peripheral nerves. This form of neuromodulation has demonstrated strong effects on neuroplasticity, leading to improvements in sensory, motor and autonomic functions, even in individuals with clinically complete SCI.^15–17^ Epidural stimulation can enhance voluntary movement amplitude in paralysed limbs and reduce spasticity in patients with incomplete SCI.^15
18–22^ However, its invasive nature and high cost have slowed down its translation into clinical practice.

In contrast, transcutaneous spinal cord stimulation (tSCS), a non-invasive approach, may target similar neural circuits and has demonstrated improvements in motor function.^21^ The mechanisms of action of tSCS are still not fully identified. One hypothesis is that spinal stimulation lowers the activation threshold of spinal motoneuronal pools, thereby enhancing the integration of residual descending supraspinal commands and segmental afferent inputs within spinal neuronal circuits to facilitate voluntary motor output.^21–23^ Recent evidence further shows that the effect of tSCS goes beyond the local spinal networks and extends into supraspinal neuronal networks.^24
25^ The posterior placement of tSCS electrodes relative to the spinal cord likely activates large-diameter sensory afferents near their dorsal root entry zones, providing robust afferent input to both spinal and supraspinal circuits. This stimulation may increase the excitability of sensorimotor networks, strengthen transmission through spared dorsal column pathways projecting to the primary somatosensory cortex (S1) and facilitate the integration of repeated sensory inputs arising from concurrent activity-based therapies.

Growing evidence supports the feasibility and potential efficacy of an approach combining ABT and cervical tSCS in individuals with long-standing SCI (chronic SCI).^26^ However, the integration of tSCS into clinical rehabilitation, particularly for individuals with subacute SCI, remains limited and understudied. To address this gap, the Neuromodulation and Intensification Research Clinic (CIME programme) was established at the Institut de réadaptation Gingras-Lindsay de Montréal (IRGLM)—one of only two specialised SCI rehabilitation centres in Quebec and the one serving the largest patient population. This research clinic was designed to implement early, intensive and personalised rehabilitation programmes that combine neuromodulation techniques, such as tSCS, with evidence-based ABT from admission (approximately 1-month post-injury) through the intensive rehabilitation phase. In that context, the upper limb project of the CIME programme is a randomised controlled trial (RCT) designed to compare the effect of cervical tSCS combined with ABT to an equivalent dose of ABT without stimulation in in-patients with subacute SCI. Individuals with SCI exhibit varying needs depending on the phase of recovery—acute, subacute or chronic—due to distinct pathophysiological processes and rehabilitation goals associated with each phase. The first few months after a SCI, when most intensive rehabilitation occurs, may capitalise on an enhanced window for experience-dependent plasticity^27^ to accelerate recovery and minimise maladaptive outcomes.

### Trial objectives

The overall objective of this RCT is to determine the effect of a supplemental intervention combining cervical tSCS+ABT on upper limb motor recovery, compared with supplemental ABT alone, in individuals with subacute cervical SCI undergoing standard in-patient rehabilitation. Participants will receive 20 intervention sessions, administered three times per week over 6–8 weeks, in addition to their usual care. Assessments will be conducted at baseline (pre-intervention), immediately post-intervention and at a 1-month follow-up. The primary outcome measure is the Upper Extremity Motor Score (UEMS) from the International Standards for Neurological Classification of Spinal Cord Injury (ISNCSCI), an established indicator of upper limb motor impairments.

### Secondary objectives

To determine the safety of the intervention (ie, minor and major adverse events (AEs)).To determine changes in sensory and motor function measured by functional clinical assessments.To explore the neuroplastic effects of the ABT+tSCS training programme on:Spinal circuits, assessed via transpinal-evoked potentials (TEPs) using single-pulse tSCS;Corticospinal pathways, assessed via motor-evoked potentials (MEPs) using transcranial magnetic stimulation (TMS);Somatosensory pathways, assessed via somatosensory-evoked potentials (SSEPs) using electroencephalography (EEG).

We hypothesise that ABT+tSCS training will lead to greater improvements than ABT alone in the primary and secondary clinical and neurophysiological measures.

## Methods and analysis

### Design and setting

A single-centre, double-blind, two-arm RCT will evaluate the impact of the CIME programme (figure 1 displays the study flow). This study is part of a larger project aiming to co-develop and implement a Neuromodulation and Intensification Research Clinic for people receiving in-patient rehabilitation after a SCI.^28^ Participants will be randomly stratified and assigned to an intervention group (n=20) or control group (n=20). The intervention group will receive 20 sessions of tSCS combined with 45 min of active ABT over 6–8 weeks. The control group will follow the same treatment schedule but with sham (placebo) stimulation. Outcomes will be measured and analysed across these time points: before the training (T1), immediately after (T2) and 1 month following the end of the intervention (T3).

**Figure 1 F1:**
[figure not shown]
Flow diagram of Neuromodulation and Intensification Research Clinic (*CIME)* Upper Limb study with design and illustration of experimental and control groups’ allocation. ABT, Activity-based therapy; tSCS, transcutaneous spinal cord stimulation.

The data collection will take place at the IRGLM of Santé Québec Centre-Sud-de-l’Ile-de-Montréal - Universitaire, Québec, Canada. The IRGLM is a site of the Centre for Interdisciplinary Research in Rehabilitation of Greater Montreal and a 153-bed academic hospital specialising in rehabilitation for individuals with physical disabilities. As one of only two centres in Quebec specialising in SCI rehabilitation, IRGLM offers both in-patient and out-patient rehabilitation organised in two programmes (functional intensive rehabilitation and rehabilitation focused on social reintegration) and provides a strong foundation for feasible participant recruitment.

### Recruitment and consent

Participants will be recruited from the SCI units at the IRGLM from 1 September 2026 to 31 August 2028. Potential eligible participants will be identified by clinicians based on the inclusion and exclusion criteria (presented in table 1) and referred to the study team. Criteria will be reviewed by the research team. Given the haemodynamic instability frequently observed during the acute phase following SCI,^29^ some individuals may be ineligible for enrolment in the CIME trial, either temporarily or permanently. Clearance from the treating medical team will be obtained prior to enrolment.

**Table 1 T1:** Inclusion and exclusion criteria

Inclusion criteria	Exclusion criteria
Traumatic and non-traumatic spinal cord injury	Cardiac pacemaker
Receiving in-patient rehabilitation	Active cancer at the stimulation site or metastatic cancer
Age≥16 years	Unstable lesion or clinical condition (eg, respiratory issues)
American Spinal Injury Association (ASIA) grade A–D	Electrode placement is impossible due to unhealed wound or significant local pain
Neurological level of injury between C5 and T2	Other neurological conditions (eg, stroke, Parkinson’s)
Residual upper limb motor impairments	Chronic liver or kidney disease
	Uncontrolled psychiatric condition
	Life expectancy<6 months
	Inability to provide informed consent (ie, severe cognitive impairment, dementia or Alzheimer’s disease)

Note: Participants with specific contraindications to transcranial magnetic stimulation, for example, epilepsy, unhealed skull fracture and increased intracranial pressure may participate in the study but will not take part in the transcranial magnetic stimulation assessment.

Once eligibility of the patient is confirmed, a clinician not involved in the research team will ask the patient whether they would be interested in hearing about a research project focusing on upper limb training. If the patient expresses an interest in hearing more about the study, a research coordinator will inform the patient of the nature of their participation and the risks and inconveniences and provide all information in oral and written form. Once the patient has given their written informed consent, they will be scheduled for their initial assessment session (see consent form in online supplemental material).

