#### Primary measures

##### Primary outcome measure

*Upper limb strength:* The UEMS of the ISNCSCI aims to manually assess muscle strength at each metameric level using a scoring system from 0 to 5. Specific muscle actions are tested to represent each level: elbow flexion for C5, wrist extension for C6, elbow extension for C7, middle finger flexion for C8 and fifth finger abduction for T1. The scores range from 0 (no visible or palpable muscle contraction) to 5 (normal active movement, full range of motion against gravity and full resistance). The UEMS demonstrates excellent inter-rater reliability (intraclass correlation coefficient (ICC): 0.99) and a moderate to good validity (Spearman coefficient r=0.91).^36–38^

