#### Training: transcutaneous spinal cord stimulation

*Skin preparation and electrode configuration:* Prior to stimulation, the skin over the stimulated area will be cleaned with isopropyl alcohol. Once dried, the area will be prepared with Tape Skin Prep Electrode (Red Dot Trace Prep, 3M Canada) to reduce skin-electrode impedance. A single or two self-adhesive cathode electrodes (Dura-Stick plus double wire or ROHVEMJ transcutaneous electrical nerve stimulation electrodes) will be placed either along the midline or paravertebral region (still covering the midline), depending on potential significant asymmetries in the motor abilities of each participant. The electrodes will span the C4 to T1 vertebral levels at first to try and facilitate activity from any motoneuronal pool. In participants with better recovery, the electrode will only cover more caudal parts depending on what muscle needs to be facilitated. A pair of reference anodal self-adhesive electrodes will be placed bilaterally on the external part of the clavicular regions. All electrodes will be secured with elastic adhesive bandages (Tensoplast, BSN Medical-Essity, Sweden) to ensure optimal skin contact.

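### Table 1 admits neurological levels down to T2 and sets no limit on time since injury, so eligibility does not match the stated subacute cervical population or the myotomes that the UEMS scores

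*Protocol article*

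**What the plan says.** The population is described in two ways.

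- **Abstract, Methods and analysis:** "We will enrol 40 individuals with cervical spinal cord injury receiving in-patient rehabilitation (20/group").
- **Trial objectives:** the effect is to be determined "in individuals with subacute cervical SCI undergoing standard in-patient rehabilitation". The Introduction treats cervical injury as synonymous with tetraplegia.
- **Table 1 (Recruitment and consent):** the level criterion is "Neurological level of injury between C5 and T2". The nearest thing to a timing criterion is "Receiving in-patient rehabilitation". A separate line requires some remaining motor impairment of the upper limb, with no threshold and no named scale.
- **Primary outcome measure:** the UEMS scores five actions from 0 to 5, namely "elbow flexion for C5, wrist extension for C6, elbow extension for C7, middle finger flexion for C8 and fifth finger abduction for T1".

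The Introduction puts admission to the programme at about one month after injury. This describes the programme and is not an eligibility rule. The same section says that the acute, subacute and chronic phases differ in pathophysiology and in rehabilitation goals. Recruitment and consent states that clinicians identify patients from the criteria in Table 1, so Table 1 is the list that decides who enters.

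**The concern.** Followed exactly, Table 1 can admit three kinds of participant whom the stated question does not cover or the primary outcome cannot inform: people whose injury is not cervical, people already at the maximum UEMS, and people who are not subacute.

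The level criterion is a contradiction between two parts of the same document. It is not detail left to a later plan. A participant at the UEMS maximum cannot show improvement in either arm, and so contributes nothing to a between-group difference in gain. The timing gap matters for a different reason. The trial is justified by the lack of evidence in subacute injury, set against growing evidence in chronic injury. If subacute is not defined at entry, the population to which the result applies is not defined either.

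**Working it through.** No plan figure settles this point, so the check sets the passages side by side.

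**Step 1: level against population.** Eligible levels in Table 1: C5, C6, C7, C8, T1, T2 (six). Cervical levels among them: C5 to C8 (four). Two of the six, T1 and T2, are therefore outside the population named in the abstract and objectives. This counts levels, not participants.

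**Step 2: level against outcome.** Myotomes scored by the UEMS: C5, C6, C7, C8, T1 (five). The eligible level T2 has no scored myotome, and all five scored myotomes lie above it. (T1 here is the thoracic level, not the baseline visit that the protocol also labels T1.)

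**Step 3: does the impairment criterion close the gap?** Table 1 criteria apply jointly, so a T2 patient with no arm weakness is excluded. The gap that remains is an impairment that the UEMS does not score. The protocol itself treats such muscles as training targets: the strengthening section of Table 3 lists shoulder flexors or abductors and the scapula, and none of the five UEMS actions tests these. Five actions at up to 5 points give a maximum of 5 × 5 = 25 per arm. A person with shoulder weakness only can score 25 in each arm, still have a residual upper limb impairment, and meet Table 1. No criterion requires a baseline score below the maximum.

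**Step 4: time since injury.** Limits in days or months in Table 1: none. The only proxy is in-patient status. Design and setting says that the site offers in-patient and out-patient care in two programmes, one intensive and one aimed at social reintegration. In-patient status therefore does not by itself fix the phase of injury, and a late or repeat stay satisfies the wording.

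**Step 5: can the effect on power be sized?** The Power calculation section needs about 34 completers and allows for about 15% attrition: 34 / (1 − 0.15) = 40, which reproduces the recruitment target. To turn Steps 1 to 4 into a loss of power one would need the share of participants who cannot change on the UEMS, and how much outcome variance they contribute. The documents give neither.

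**The case against.** The strongest reply is that the criteria work together. If a T2 lesion lies below every scored arm muscle, a T2 patient will usually have no arm weakness and will fail the impairment criterion, so the T2 wording may be almost inoperative. This largely stands: it makes ceiling cases uncommon. It does not remove the contradiction with the cervical population, and Step 3 shows a route that stays open.

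The second reply is that subacute is carried by the setting: recruitment is from in-patient spinal units, admission is about a month after injury, and a fuller protocol may hold a definition. It is fair that most participants will probably be early after injury, and nothing in the documents suggests that late stays are frequent. Even so, the article presents Table 1 as the criteria that clinicians apply, and the table leaves the phase open. The timing part is therefore weaker than the level part, but it remains.

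Three stronger readings are tempting and are not supported:

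- **Chronic participants would dilute the effect.** The abstract says that the benefit of the combined therapy has been shown particularly in chronic cervical injury, and the Introduction cites growing evidence there. They cannot be counted as non-responders. The issue is applicability.
- **A specific number of participants is lost.** Any effective sample size would rest on an invented share and on an assumption that people who cannot change still contribute full variance.
- **Days since injury should have been stratified or must be in the model.** Randomisation protects the comparison without it, and 24 strata for 40 participants are already sparse. A days-by-visit term would also cost parameters in a small trial.

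**Conclusion.** The point holds as a wrong-as-written eligibility rule. Table 1 contradicts the abstract and objectives on level, admits one level that the primary outcome does not score, and leaves subacute without an operational criterion. The size in terms of power is unknown. The impairment criterion probably keeps the number of ceiling cases low, and the documents do not show how many T1, T2, late or repeat in-patients would be referred.

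A reader might infer that the trial can no longer answer its question. That goes too far: a sample made up mostly of early in-patients with cervical injury would still answer it. What can be said is that the plan does not guarantee such a sample. The conclusion rests on reading Table 1 literally and as the complete screening list, which is how the article presents it.

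**What to change.** Amend before recruitment opens on 1 September 2026:

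1. Reconcile the level criterion in Table 1 with the cervical population and the UEMS myotomes. If lower levels are intended, restate the population in the abstract and objectives instead.
2. Tie the impairment criterion to the primary outcome by requiring a baseline UEMS below its maximum.
3. Add a time-since-injury criterion using the sponsor's own definition of subacute, and state it in the article.

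Days since injury may be prespecified as a covariate for precision. This is optional and uses degrees of freedom in a trial of about 34 completers.

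The cost is an amendment submitted for ethics approval and a few referrals that become ineligible. Randomisation, visits and the analysis model need not change.

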### Randomisation method and blinding

Forty participants who meet the inclusion criteria will be randomly assigned to either the intervention or control group. An independent statistician will generate the stratified randomisation sequence using Stata 16. Stratified randomisation with a 1:1 allocation ratio will be used to ensure balance across key characteristics, including age, sex and SCI severity as classified by the American Spinal Injury Association (ASIA). These variables were selected a priori because they are clinically important prognostic factors known to influence recovery and functional outcomes after SCI and imbalance across groups could bias treatment effect estimates. We acknowledge that the number of potential strata is relatively large compared with the target sample size (n=40), which may result in sparse strata. To address this, a restricted randomisation approach will be used (eg, permuted block randomisation). In addition, baseline characteristics will be carefully assessed, and any residual imbalance in key variables (particularly SCI severity) will be adjusted for in the primary analysis. This will be done in collaboration with the statistician on the team. This approach balances the need to control for important prognostic factors with the practical constraints of a small sample. Randomisation will occur after the initial assessment (T1). Neurological level and injury severity will be determined using the ISNCSCI,^30
31^ with impairment categorised according to the ASIA Impairment Scale, ranging from A (complete injury with no sensory or motor function preserved in sacral segments S4–S5) to E (normal function). Age will be categorised into three groups: 16–34 years, 35–49 years and 50+ years. Sex will be categorised into two groups: male and female. These variables were selected for stratification due to their potential influence on outcomes and to minimise confounding effects.^32–35^ To maintain balance in recruitment over time, permuted block randomisation will be employed with block sizes of 4 or 6. This approach will ensure equal distribution of participants between the intervention and control groups within each block, thereby reducing the risk of imbalance as the study progresses. The permutation of blocks will randomise the order of allocation, further enhancing the reliability and reproducibility of the randomisation process. A total of 40 participants will be included in the randomisation process to account for potential dropouts before the completion of the study (see section Power calculation). Consequently, 24 separate randomisation lists or *strata*, each containing 40 participants, will be generated based on the stratification variables. All study personnel involved in the clinical assessments will remain blinded to the group allocation. Participants will also remain blinded to their assigned group throughout the study. The interventionist will not be blind to the group allocation due to the immediate effect of tSCS.

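### Permuted blocks of 4 or 6 inside 24 strata cannot be relied on to balance 40 participants on arm size or AIS grade, so blocking is no remedy for the sparse strata

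*Protocol article*

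**What the plan says.** Under Design and setting, the article gives the target split: "Participants will be randomly stratified and assigned to an intervention group (n=20) or control group (n=20"). Under Randomisation method and blinding it gives the total, "Forty participants who meet the inclusion criteria will be randomly assigned to either the intervention or control group", and the purpose of stratifying: "Stratified randomisation with a 1:1 allocation ratio will be used to ensure balance across key characteristics, including age, sex and SCI severity".

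The strata follow from that section and Table 1. "Age will be categorised into three groups: 16–34 years, 35–49 years and 50+ years". "Sex will be categorised into two groups: male and female". Table 1 admits AIS grades A to D. The article itself states that this makes 24 separate lists. On each list, "permuted block randomisation will be employed with block sizes of 4 or 6".

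The same section concedes that the strata are many for 40 people and may be sparse. It offers two responses. The first is blocking: "To address this, a restricted randomisation approach will be used (eg, permuted block randomisation"). The second is to inspect baseline characteristics and adjust the primary analysis for residual imbalance, SCI severity above all. On what blocking achieves, it says: "This approach will ensure equal distribution of participants between the intervention and control groups within each block", and that this lowers the risk of imbalance.

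**The concern.** A permuted block forces equal numbers only once every place in it is used. Sparse strata are the strata in which blocks stay open, so blocking is offered as the answer to the very condition that defeats it. The sentence about equality within each block is true of completed blocks, but few blocks in this trial will be completed.

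What is at stake is balance on AIS grade, the factor the article singles out. It says these factors influence recovery and that imbalance in them could bias the estimated effect. With about 20 people per arm, a grade that differs by four or more between arms is a visible imbalance. The planned 20:20 split is also not secured, although that matters much less.

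**Working it through.** **1. The plan's own figure.** 3 ages × 2 sexes × 4 AIS grades = 24 lists, which reproduces the stated number. The mean per list is 40/24 = 1.67, less than half of the smallest block (4/2 = 2).

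**2. How many lists can fill a block.** Whatever the case mix, at most 40/4 = 10 of the 24 lists can reach four people, so at least 14 can never complete a block.

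For expected numbers a case mix is needed, and the article gives none. Two are assumed:
- even: probability 1/24 per stratum;
- skewed: ages 20/20/60%, 75% of one sex, AIS A–D 20/12/18/50%.

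With p the probability of a stratum, the chance that its list stays below four is the sum over k = 0 to 3 of C(40,k) p^k (1−p)^(40−k). Summed over the 24 lists, this gives 22.0 lists (even) or 20.7 (skewed). Of the lists that receive anyone, 18.9 of 19.6 (even) or 14.4 of 15.3 (skewed) end with an open block.

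**3. Balance by simulation.** 20,000 trials of 40 people per scheme, with block sizes of 4 or 6 chosen at random. Minimisation used the three factor margins with probability 0.8 for the better-balancing arm. Results are even / skewed.

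| Scheme | 22:18 or worse | Some AIS grade differs by ≥4 |
|---|---|---|
| 24 lists, as planned | 53% / 47% | 48% / 32% |
| Simple randomisation | 64% / 63% | 72% / 67% |
| Blocks by AIS grade only | 12% / 13% | 0% / 0% |
| Minimisation | 7% / 7% | 10% / 8% |

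Under the plan, 23:17 or worse occurs in 30% / 23%, and exactly 20:20 in 17% / 19%.

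Repeat runs, including a second skewed mix (75% male, ages 25/20/55%, AIS A–D 25/10/20/45%), gave:
- as planned: 53–54% / 47–48% for 22:18 or worse, and 48% / 33–34% for AIS;
- simple randomisation: 64–65% and 69–71%;
- minimisation: 8–10% and 13–15%. Its result depends on how the imbalance score is defined.

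The 0% for AIS-only lists holds by construction. Each list has at most one open block, and an open block of 6 can be out by at most 3.

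**4. Cost in precision.** For arm size alone, effective N = 4·n1·n2/40. This is 4·22·18/40 = 39.6 at 22:18 and 4·24·16/40 = 38.4 at 24:16. Summing 4·n1·n2/(n1+n2) over AIS grades gives the effective N after adjusting for grade. It averages about 37.5–37.8 as planned and 39.3–39.6 with AIS-only lists, roughly 4–5% lower under the plan.

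**5. What AIS-only lists give up.** Some age group differs by 4 or more between arms in 51% with AIS-only lists and 51% as planned (even mix), and in 49% and 40% (skewed mix).

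**The case against.** Several stronger readings are tempting, and the article does not support them.

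- *The scheme cannot balance the arms.* It sometimes does: exactly 20:20 in 17% / 19% of simulated trials, and 21:19 or better in 100 − 53 = 47% or 100 − 47 = 53%. The accurate statement is that it cannot be relied on.
- *It is no better than simple randomisation.* On arm size it is not far off, but on AIS grade it is clearly better: 48% against about 71% (even mix), and about 33% against 69% (skewed).
- *The article promises balance outright.* It gives balance as the purpose of stratifying, claims equality only within blocks, and openly allows for residual imbalance.
- *The randomisation is invalid or the estimate biased.* It is neither. Chance imbalance does not bias the estimator over repetitions, and unequal arms by themselves cost almost nothing.

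The best defence is the planned adjustment for residual imbalance, and it carries some weight. It is, however, conditional on what is observed at baseline, and the model under Statistical analysis lists only group, time, their interaction and a participant effect. A separate analysis plan may add terms. Even so, with complete data, an AIS main effect leaves the group×time estimates unchanged; only an AIS×time term would alter them. Adjustment also cannot restore balance by design.

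It is also fair to say that the probabilities rest on assumed mixes and that minimisation against stratified blocks is partly preference. The conclusion is nevertheless the same under every mix tried. AIS-only blocks keep the article's own method and do better on its own priority.

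**Conclusion.** The point holds in this form: the stated remedy for sparse strata is wrong as written, and the scheme cannot be relied on for the 20:20 split or for balance on AIS grade. The list count and the mean of 1.67 come from the article itself. The imbalance probabilities depend on assumed case mixes, and the even mix gives the worse figures. The harm is lost prognostic balance plus roughly 4–5% of effective sample size. This should be fixed before allocation starts, but it does not threaten the validity of the trial.

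**What to change.** Before the first allocation, replace the 24 lists with one of these:

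- **Permuted blocks stratified by AIS grade only**, with age and sex handled as prespecified covariates. Because the primary test is group×time, the analysis text should say how the covariates enter that contrast.
- **Minimisation on AIS grade, age group and sex with a random element**, for example probability 0.8 for the better-balancing arm.

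In either case, delete the statement that permuted blocks address sparse strata.

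The cost is regenerating the sequence, which an independent statistician already produces, before recruitment opens on 1 September 2026. AIS-only lists give up design balance on age and sex, but little is lost because the 24 lists barely provide it. Minimisation needs central, real-time allocation. Once participants have been randomised, the change can no longer be made cleanly.
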